## Abstract

Patients diagnosed with malignancy, neurological and immunological disorders, *i.e.*, fragile patients, have been excluded from COVID-19 vaccine trials. However, this population may present immune response abnormalities, and relative reduced vaccine responsiveness. Here we review the limited current evidence on the immune responses to vaccination of patients with different underlying diseases. To address open questions we present the VAX4FRAIL study aimed at assessing immune responses to vaccination in a large transdisease cohort of patients with cancer, neurological and rheumatological diseases.

## Immune Responses Of Fragile Patients: Current Evidence

Main results from current available studies evaluating the immune response in fragile subjects, represented by humoral response in most of the cases, are summarized in **Table 1**. Overall, anti-SARS-CoV-2 antibody response rates in patients diagnosed with malignancies and/or disease requiring immunosuppressive therapies, was considerably low. Specifically, SARS-CoV-2 antibody responses at week 3 following the first dose of the Pfizer BioNTech vaccine were only 39% and 13% in patients with solid and hematological malignancies respectively, compared with 97% in those without cancer (6). After the second dose, the immune response improved significantly for solid tumor patients, with 95% of them showing detectable antibodies to the SARS-CoV-2. By contrast, those who did not get a vaccine boost at three weeks did not display any real improvement, with only 43% of solid tumor patients and 8% of hematologic cancer patients developing antibodies. The poor response to one single dose of vaccine was also confirmed in patients with multiple myeloma and in solid transplant recipients (7, 8). Finally, although the guidance for patients receiving chemotherapy and needing vaccines has been relatively clear so far, it is not yet so for anti-COVID-19 vaccination. In fact, an initial report indicated that vaccine non-responders were also somewhat more frequent among those who received vaccination within 15 days of cancer treatment, particularly chemotherapy (6). This finding needs to be corroborated in order to optimize the timing of vaccination while preserving the anti-cancer treatment schedule. Questions regarding the interference of treatment and disease in seroconversion and anti-SARS-CoV2 vaccine efficacy extend to several other conditions not only related to cancer (6, 7, 9, 10), but including also immunological disorders (8, 9) and disease requiring immunosuppressive therapies (8, 13–15). It is therefore paramount, particularly in the current pandemic situation, to identify a methodology to address key issues about immunogenicity (e.g. the kinetic of immune response and its persistence, the neutralization capability of specific antibodies, the coordination of both humoral and cell-mediated immune responses) to optimize monitoring protocols in the highly complex fragile patient populations. It is also fundamental to evaluate whether some fragile conditions do not allow proper vaccination and these patients should therefore wait to be vaccinated or be protected differently as for instance by creating a ring of protected relations, or should receive a third boosting dose. It is also imperative to assess whether the vaccination schedule should take into account patient treatments and be delayed to avoid interference. In a time of vaccine scarcity, these issues are important for a proper vaccination national plan. A comprehensive study of the immune response in fragile patients will allow in the future to take informed decisions on the questions raised above.

**Table 1 T1:** Immune responses of fragile patients: current evidence.

Author	Disease	Vaccines	n	Immune assessment	Timing of assessment		Vaccine responders	Comments
					1^ dose (n)	2^ dose (n)		
Monin-Aldama L, 2021 (5)	Solid and haematological malignancies	BNT162b2	151	Antibody seroconversion, T cell responses, and neutralisation of SARS-CoV-2 Wuhan strain and of a variant of concern (B.1.1.7)	X (118)	X (30)	15%-40%	Efficacy increased by boosting at 21-days (95% within 2 weeks of boost) in solid cancer patients .
Bird S, 2021 (6)	Multiple Myeloma	BNT162b2	93	SARS-CoV-2 IgG antibodies directed against the Spike-protein	X (93)		70%	
		ChAdOx1 nCoV-19						
Boyarsky BJ, 2021 (7)	Organ transplant	BNT162b2mRNA-1273	436	SARS-CoV-2 IgG antibodies directed against the Spike-protein	X (427)		31% (BNT162b2)	Increased antibody response in young, in absence of immunosuppressive therapy, and with mRNA-1273.
							69% (mRNA-1273)	
Herishanu Y, 2021 (8)	CLL	BNT162b2	167	SARS-CoV-2 IgG antibodies directed against the Spike-protein		X (167)	39.5%	Vaccine responders: 79.2% among complete disease responders, 55.2% in treatment-naïve, and 16% in patients under treatment.
Agha M, 2021 (9)	Haematological malignancies	BNT162b2	67	SARS-CoV-2 Ig Ma and IgG antibodies directed against the Spike-protein		X (67)	54%	
		mRNA-1273						
Wong SI, 2021 (10)	Inflammatory bowel disease	BNT162b2	48	SARS-CoV-2 IgG antibodies directed against the Spike-protein, and Nucleocapsid-protein	X (22)	X (26)	71.4 and 100% after the 1^ and 2^ dose	Decreased antibody titers in patients receiving anti-TNF therapies.
		mRNA-1273						
Geisen UM, 2021 (11)	CID	BNT162b2	26	SARS-CoV-2 IgG antibodies directed against the Spike-protein; neutralising antibodies ELISA-based neutralisation test system; SARS-CoV-2 IgA antibodies		X (26)	100%	IgG titres lower in patients with CID as compared with healthy controls. No patients experienced flare up of CID.
		mRNA-1273						
Rabinowich L, 2021 (12)	Organ transplant	BNT162b2	80	SARS-CoV-2 IgG antibodies directed against the Spike-protein, and Nucleocapsid-protein		X (80)	47.5%	
Grupper A, 2021 (13)	Organ transplant	BNT162b2	136	SARS-CoV-2 IgG antibodies directed against the Spike-protein		X (136)	37.5%	
Chavarot N, 2021 (14)	Organ transplant	BNT162b2	101	SARS-CoV-2 IgG antibodies directed against the Spike-protein	X (101)	X (35)	2% and 5.7% after the 1^ and 2^ dose	
		mRNA-1273						

CLL, Chronic lymphocytic leukemia; CID, Chronic inflammatory diseases.

## Challenges

One of the problems in designing a study on fragile subjects is that the in-scope population is very dis-homogeneous and running double blind randomized studies would pose at least two challenges. One challenge would be the number of stratification factors and the sample size required for a study sufficiently powered to provide conclusive results. The second, but not less relevant, challenge would be ethical as in the presence of an approved vaccine it would be difficult to offer only placebo to a subject who could potentially benefit of an intervention. Given the difficulties in studying these specific situations it is quite understandable why, thus far, no MAH (marketing authorization holder) has initiated any specific study and has left to the health authorities/treating physician the final benefit/risk recommendation for the single individual.

To better understand the type of immunologic response elicited by the vaccination in selected subgroups it is important to define the different categories to be studied. Firstly, some immunologic conditions are *per se* criteria for an altered immunocompetence such as for instance the clinical situation of patients receiving organ or bone marrow transplants and thus needing immunosuppressive therapy. Secondly, patients with a diagnosis of cancer are another subgroup which for different reasons may have alterations of their immune response and which can be further segmented in patients with advanced solid tumors (recurrent, metastatic, extended solid tumors), patients with a diagnosis of cancer (solid tumors) not necessarily advanced but under treatment (for instance chemotherapy but also antibody drug conjugates and or either immune therapies and or cell therapies) and patients with hematologic malignancies.

## Objectives

In the context of the national vaccination campaign in which available vaccines are administered to fragile patients, this study would like to assess prospectively the effectiveness of the COVID-19 vaccination in these specific subgroups, and to characterize the kinetics of the immune response to the vaccination and its persistence overtime. Here we have gathered together 12 healthcare centers recognized as centers of excellence by the Italian Ministry of Health (Istituti di Ricovero e Cura a Carattere Scientifico, IRCCS) to share one common protocol of vaccine assessment that has centralized the testing of antibody responses, and their neutralizing activities, and has shared common reagents and technologies for the evaluation of the T cell response to the Spike vaccine protein (**Figure 1**). Hopefully, the characterization of the subgroup responses will allow to shade some light on the true efficacy of the COVID-19 vaccination in the so called altered immunocompetent population.

**Figure 1 f1:**
[figure not shown]
Organogram of the clinical study.

## Study Design

The VAX4FRIAL study is an observational, multicentre, prospective study with the general objective is to assess the effectiveness of the COVID-19 vaccination in terms of induction of humoral and cell-mediated immune responses in selected fragile (altered immunocompetence) populations, due to their underlying conditions or therapeutic treatments. It will be conducted through the creation of a network between 12 IRCCS in Italy. The study will be carried out in compliance with the Helsinki Declaration. The protocol has been approved by national competent authorities (AIFA) and the ethics committee of National Institute for Infectious diseases Lazzaro Spallanzani (IRCCS), and has been registered in ClinicalTrials.gov (NCT04848493). All patients will sign written informed consent before being enrolled for the study. We also recommended that COVID-19 vaccination studies activated independently by each institution shared the same outline as VAX4FRAIL. This recommendation was made to allow for the possible pooling of data from eligible cases not originally included in the VAX4FRAIL study.

## Participants

The study design plans to recruit 1300 fragile patients, divided among the following subgroups: 1) patients affected by hematological malignancies (n= 500); 2) patients affected by solid tumors (n= 400; 3) patients affected by immunorheumatological diseases, as ANCA-associated vasculitis and interstitial lung disease in autoimmune conditions (n=200 patients); 4) patients affected by neurological diseases, as multiple sclerosis and generalized Myasthenia Gravis (n=200 patients).

## Inclusion Criteria

i) Age ≥ 18 years, ii) undergoing COVID-19 vaccination with Pfizer-BioNTech or Moderna vaccine; iii) life expectancy of at least 12 months at the time of vaccine administration, according to the clinician’s evaluation; iv) Ability to understand and the willingness to sign a written informed consent document; v) Signed Informed Consent Form.

## Exclusion Criteria

i) Patients with psychiatric illness/social situations that would limit compliance with study requirements; ii) History of laboratory-confirmed SARS-CoV-2 infection.

A hemogram will be performed for each patient before vaccination to evaluate the baseline levels of neutrophils, lymphocytes and monocytes. A control group of subjects without evidence of specific disease will consist of 300 Health Care Providers collected by IRCCS Spallanzani, Rome, receiving the same vaccination treatments, and assessed for humoral and cell-mediated immune responses with the same procedures of this protocol.

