## Procedures

According to the national and regional indications, patients enrolled in this study will be vaccinated with either the Pfizer/BioNTech or with Moderna vaccines. Patients will be monitored for antibodies and cellular immunity directed against the SARS-CoV-2 spike antigen for 12 months or until death. In particular, blood samples for immunological testing will be performed at 6 time points (**Figure 2**) as follows: T0, the day of vaccination; T1, the day of the booster dose (according to the schedule of the vaccines: 3 weeks after T0 for patients receiving Pfizer/BioNTech vaccine, 4 weeks after T0 for patients receiving Moderna vaccine); T2, between 5 and 7 weeks after T0 for patients receiving Pfizer/BioNTech vaccine and between 6 and 8 weeks after T0 for patients receiving Moderna vaccine; T3, 12 (± 1) weeks after T0; T4, 24 (± 2) weeks after T0; T5, 52 (± 2) weeks after T0.

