## Immunological Efficacy Assessment

Humoral response: For each time point the humoral immune response to vaccination will be assessed by a serological assay able to detect anti-Spike IgG antibodies in sera Possible natural infection before or after vaccination will be assessed by measuring anti-Nucleocapsid IgG antibodies. Patients with potential concurrent SARS-CoV-2 infection identified through anti-N increased level at the same time point will be excluded by this analysis. On a subset of subjects, at 2-4 weeks after the booster dose and at 12, 24 weeks after first vaccine administration, a neutralization assay will be performed to evaluate the functional activity of vaccination induced anti-Spike antibodies. Briefly, sera from patients will be tested for their ability to neutralize SARS-CoV-2 infection of VERO-E6 cells in a BSL-3 facility.

T cell immunity: The cell-mediated immune response to vaccination will be assessed by a first-line test standardized on whole blood assay. Briefly, at the laboratory of each clinical center heparin blood samples will be stimulated in the absence/presence of a pool of peptides spanning the S protein (S: PepTivator^®^ SARS-CoV-2 ProtS, PepTivator^®^ SARS-CoV-2 ProtS1; PepTivator^®^ SARS-CoV-2 ProtS+, purchased by Miltenyi Biotech) for 20 hours at 37°C 5%CO2. The day after, conditioned plasma will be harvested and stored to quantify the release of IFNγ, TNFα, IL-2 and IP-10 cytokines by automated Immunoassay assay (Protein Simle, Biotechne). Moreover, peripheral blood mononuclear cells (PBMC) will be isolated and stored to allow subsequent other T cell assay (e.g., ELISpot assay).

All serological assays, quantification of released cytokines in conditioned plasma and ELISpot assay will be centralized in the Spallanzani laboratory to generate homogeneous data by sharing reagents and technologies.

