## Data Collection

A standard electronic case report form (e-CRF) will be designed at the beginning of our study by the Fondazione IRCCS Istituto Nazionale dei Tumori, Milano Clinical Trial Center. It will be used to obtain demographic information, disease history, surgical details, imaging features and outcome events of participants. Following registration, patient data will be collected in the e-CRF. Clinical and centrally collected and processed laboratory data will be analysed by the study sponsor IRCCS Reggio Emilia.

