## Sample Size

In this context of high uncertainty on short- and long-term effect of vaccination, the approach to this observational study will be mainly descriptive and based on confidence intervals rather than hypotheses testing. According to immunological tests on a sample of 250 Health Care Providers analysed in the laboratories of the IRCCS Regina Elena, Rome, the geometric mean titer after one week from the second vaccine administration was about 286 AU/ml with a 95% confidence interval ranging from 250 to 328.

As an indication of how many patients we could include for each subgroup we may consider the use of the Student t-test on logarithm of concentration to assess differences in titer at a specific time-point between subgroups of patients and subjects without evidence of disease.

Under these assumptions a sample size of 100 patients for each subgroup will allow to assess differences in terms of geometric mean of titers of about 80 AU/ml with a power of 80% at a significance level of 5% when the standard deviation, on the logarithmic scale, is equal to 1.

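### The patient–control comparison names no adjustment for age, sex or vaccine product, although the controls are unmatched staff from one centre and differences are attributed to the condition

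*Protocol article*

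**What the plan says.** All section names are those of the protocol article.

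- **Controls** (Exclusion Criteria): "A control group of subjects without evidence of specific disease will consist of 300 Health Care Providers collected by IRCCS Spallanzani, Rome". No matching or balancing on age, sex or vaccine mix is stated. On comparability the article says only that this group is "receiving the same vaccination treatments, and assessed for humoral and cell-mediated immune responses with the same procedures of this protocol".
- **Patients** (Inclusion Criteria, Study Design, Procedures): the criterion is "Age ≥ 18 years, ii) undergoing COVID-19 vaccination with Pfizer-BioNTech or Moderna vaccine", with no upper age limit. There are 12 centres. Following national and regional rules, "patients enrolled in this study will be vaccinated with either the Pfizer/BioNTech or with Moderna vaccines".
- **Analysis** (Statistical Analysis): a repeated-measures ANOVA is to study the trend over time in each subgroup against the disease-free referents. No covariates are named. Analyses overall and by subgroup are meant to bring out differences tied to the particular condition.
- **Where covariates go**: Statistical Analysis gives socio-demographic factors and comorbidities to subgroup analyses. Expected Outcomes gives treatments, demographics and comorbidities to post-hoc work outside the study objectives.
- **Sizing** (Sample Size): as a guide to subgroup size only, the article considers "the use of the Student t-test on logarithm of concentration to assess differences in titer at a specific time-point".
- **Laboratory** (Immunological Efficacy Assessment): serology, cytokine quantification and ELISpot are centralised, but "at the laboratory of each clinical center heparin blood samples will be stimulated".

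**The concern.** Health-care staff in employment probably have a bounded age range, and their sex distribution may differ from that of any patient group. The article does not describe either. Patients have no upper age limit, and their vaccine follows regional supply rules. Receiving the same two products does not mean receiving them in the same proportions. If age, sex or product affects titre, the raw patient–control difference mixes those effects with the effect of disease or treatment, and the analysis section would credit all of it to the condition.

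Comparing trends over time does not escape this. At T0 there is no vaccine response yet, so a factor that alters the response appears in the group-by-time pattern just as a disease effect would.

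Subgroup analyses by socio-demographic factor show how response varies within strata. They do not correct the headline contrast. A confidence interval around that contrast, however narrow, is centred on the wrong quantity.

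**Working it through.** **Inputs from the article.** Sample Size: reference geometric mean 286 AU/ml (95% CI 250 to 328, 250 health-care providers); 100 patients per subgroup; 80% power; 5% significance; SD 1 on the log scale; detectable difference about 80 AU/ml. Participants: subgroups of 500, 400, 200 and 200. Exclusion Criteria: 300 controls. I take the test as two-sided and the log as natural; the article states neither.

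**Step 1: reproduce the plan's figure.** On the log scale, d = (1.960 + 0.842) × SD × √(1/n₁ + 1/n₂), and the difference is 286 × (1 − e^(−d)).

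- 100 vs 300: d = 0.3235, difference 79.0 AU/ml.
- 100 vs 250: d = 0.3315, difference 80.7 AU/ml.
- 100 vs 100: d = 0.3962, difference 93.6 AU/ml.

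The stated 80 AU/ml therefore reproduces with 250 or 300 controls. The SD implied by the quoted interval is ln(328/250) / (2 × 1.96) × √250 = 1.10, close to the assumed 1. There is no arithmetic error in the sizing.

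**Step 2: effect of confounding when disease has no effect.** Suppose confounding alone makes the patient/control geometric mean ratio r. With SE = √(1/n + 1/300), the unadjusted comparison at one time point rejects with probability Φ(−ln r/SE − 1.96) + Φ(ln r/SE − 1.96).

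| Patients | SE | Detectable difference (AU/ml) | r = 0.95 | r = 0.90 | r = 0.80 | r = 0.70 |
|---|---|---|---|---|---|---|
| 100 | 0.115 | 79.0 | 7% | 15% | 49% | 87% |
| 200 | 0.091 | 64.5 | 9% | 21% | 69% | 97% |
| 400 | 0.076 | 55.1 | 10% | 28% | 83% | 99.7% |
| 500 | 0.073 | 52.9 | 11% | 30% | 86% | 99.8% |

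A 10–20% shift is 286 × 0.10 = 29 to 286 × 0.20 = 57 AU/ml. The upper end is of the same order as the 53–65 AU/ml detectable at the planned sizes of 200 to 500. Larger subgroups make a spurious difference more likely to be declared.

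**Step 3: what could produce such a shift (assumptions only).** A titre 10% lower per decade with a 20-year age gap gives 286 × (1 − 0.9²) = 54 AU/ml; 5% and 10 years gives 14; 20% and 20 years gives 103. For product mix, if one vaccine gave 1.5 to 2 times the titre and the mix differed by 40 percentage points, the ratio would be 1.5^0.4 = 1.176 to 2^0.4 = 1.320. As a patient deficit this is 286 × (1 − 1/1.176) = 43 to 286 × (1 − 1/1.320) = 69 AU/ml. The direction of a product imbalance is unknown; it could equally hide a deficit.

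**Step 4: price of adjusting.** If covariates explain a share R² of the variance in group membership and none of the titre variance, d at 100 vs 300 is multiplied by √(1/(1 − R²)). R² = 0.10 gives 82.6 AU/ml and R² = 0.50 gives 105.0. Power for 80 AU/ml falls from 81% to 77% and 52%. If the covariates also explain 20% of titre variance, the range is 75–96 AU/ml.

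**The case against.** The strongest reply is that this is a condensed article, that a covariate list normally sits in the full protocol or analysis plan, and that nothing here forbids adjustment. Adjustment may indeed be specified there. But the article does more than stay silent: it gives demographics and comorbidities another role, in subgroup and post-hoc analyses, and attributes the contrast to the condition. Calling the study mainly descriptive and interval-based does not cure a confounded interval.

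Several stronger readings are tempting and are not supported:

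- **That unadjusted t-tests are the planned analysis.** The t-test is only a sizing device; Statistical Analysis does not mention it.
- **That the article's own evidence proves age and product effects here.** The Table 1 remark, "Increased antibody response in young, in absence of immunosuppressive therapy, and with mRNA-1273", comes from one row on organ-transplant recipients after a first dose, and they are not among the four subgroups. It shows that the authors had reason to consider these factors, not how large they are in this cohort.
- **That centre distorts every outcome.** Central testing limits the laboratory effect to the whole-blood stimulation done at each site, although populations may still differ between centres.
- **That the control contrast is the main result, or that subgroup rankings are distorted by it.** The article declares no main comparative result and plans no ranking, and one shared control group cannot reorder the subgroups.
- **That every covariate is already in hand.** Of the case report form the article says "It will be used to obtain demographic information, disease history", and it speaks of patient data. The visit schedule depends on the product, so product should be known for patients. Collection of these items for controls is not stated.

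**Conclusion.** The concern holds as a matter of design and interpretation. Followed as written, the plan compares unmatched staff from one centre with patients of any adult age from 12 centres, through a model with no named covariates, and assigns the difference to the disease. Vaccine product is partly dealt with because controls receive the same vaccines; a different mix remains possible.

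The size cannot be derived from the article. The false-positive rates assume a 10–20% confounding shift, a natural-log SD of 1, 300 controls and a single-time-point comparison. A 5% shift would raise the error only to 7–11%. Large true deficits would survive adjustment; the risk is greatest where the true effect is moderate or absent.

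**What to change.** 1. Make the patient–control contrast a linear or mixed model on log titre, adjusted for age, sex and vaccine product. Report it over the age range in which both groups have data, and keep the unadjusted contrast as secondary.
2. Confirm that age, sex and vaccine product are held for the controls. Where adjustment is not possible, describe the contrast as descriptive and not as an effect of the condition.
3. For the locally stimulated whole-blood assay, analyse stimulated minus unstimulated release; both are already measured. State that centre is confounded with control status. Add a same-centre sensitivity contrast only if enough patients come from the control centre, a number the article does not give. A random intercept for centre is no substitute, because it separates centre from control status only through those same patients.

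The cost is mainly analysis wording, plus retrieving control data if they are not yet held. The statistical price is a wider interval and a narrower age range: from 79 to about 83–105 AU/ml detectable at 100 vs 300, if covariates explain 10–50% of the variance in group membership and none of the titre variance. The planned subgroups of 200 to 500 leave some room for this.
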